### Objectives

Primary objective of the trial is to clarify the question of whether a risk adapted procedure in treating femoral shaft fractures in multiple trauma patients as opposed to an early definitive treatment strategy leads to an improved outcome with respect to morbidity and mortality and if yes at what costs.

Furthermore, it shall be scrutinized to what extent the choice of treatment depends on anatomic and physiologic damage severity.

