### Adverse events

All adverse events (AE) during hospital stay will be documented for both study groups. Rate of serious adverse events (SAE), e.g. mortality or ARDS incidence, are part of the secondary endpoints and will be monitored closely. Serious adverse events will be reported to the Principle Coordinating Investigator as soon as possible, at the latest within 24 hours.

Possible complications of the risk-adaptive treatment („damage control orthopedics”, DCO):

Since there are at least two interventions in this treatment arm, there is a hypothetical higher risk of infection in these patients, longer ventilation time, and a certain rate of patients in whom no change from fixateur externe to intramedullary nail is possible and thus, resulting in a higher rate of pseudarthrosis, worse functional result, delayed weight bearing and lower quality of life.

Complications of the primary definitive treatment are primarily the hypothetically higher mortality, increase in duration and rate of SIRS, sepsis and/or multi organ failure (MOF).

Expected Adverse Events

Complications of surgery include:

• Infection

• Delayed healing

• Bleeding

• Nerve injury

• Tendon and muscle injury

• Thrombosis/embolism

• Pseudarthrosis

• Compartment syndrome

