### Statistical analyses

The main outcome variable is the maximum SOFA score during ICU stay. In order to have comparable periods, the time period for SOFA score assessment is limited to the first 28 days after trauma. Documentation of daily SOFA scores is continued in intermediate care or other high dependency units.

The maximum SOFA score will be compared using non-parametric statistics (U-test) due to the substantial skewness of the distribution. Since severity of trauma is assumed to be a major determinant of outcome (including rate of organ failure) the comparability regarding Injury Severity Score (ISS) is tested before analysis. In case of substantial imbalance (p < 0.15; U-test) a stratified analysis of outcome will be performed (two groups; ISS ≤/> 30 points).

Analysis will be done according to intention to treat; regarding to the per protocol (PP) analysis we expect the PP-population to be 5% less.

There will be one interim analysis of data collection when about half of the expected sample size has been included (70 cases). The p-value for the interim analysis will be set at 0.005 so that the final analysis will be done at a significance level of 0.048, according to Fleming and O'Brien [31].

During interim and final analysis, a detailed safety analysis will be performed by comparing predicted and observed survival within each group and reviewing individual cases of non-survivors.

In addition, all secondary endpoints mentioned in the protocol will be considered for explorative analysis, because these factors are repeatedly named in the discussion about the advantages of damage control orthopedics. The aim of presenting all these data is not a confirmative statistical testing, but rather to serve as a basis for comparative analyses in future meta-analyses regarding damage control orthopedics versus early total care strategies.

The hospital perspective on costs includes the initial and all secondary operations or readmissions until one year after randomization. As most costs during hospital stay are caused by surgery itself and ICU care, data collection and statistical analysis will focus on these two aspects. The results will be reported as a cost-effectiveness analysis using life-years lost as the measure of treatment benefit. These analyses will employ decision-analytic models for the optimum management of multiply injured patients with femoral shaft fracture.

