## Discussion

Today, there is a trend towards the concept of "Damage Control Orthopedics" in the management of multiple trauma patients with long bone fractures. But, evidence from the current literature is insufficient. As discussed above, results are contradictory, a generalized management strategy is missing. Thus, in the era of "evidence-based medicine", there is the need for a more specific, clarifying randomized controlled trial. Therefore this new trial was initiated.

To our knowledge, this trial is the first to evaluate the risk adapted damage control orthopedic surgery of femur shaft fracutres in multiple trauma patients in a randomized controlled design. In 2003, Pape et al. [32] presented their results of a randomized controlled trial. They investigated the impact of intramedullary instrumentation versus damage control for femoral fractures on immunoinflammatory parameters and complications [32,33]. But, in contrast to this study, where a risk adaption is performed, they excluded multiple trauma patients with severe brain and thoracic injuries (AIS > 3) and patients in unstable or critical condition, too. In summary, the included patients were injured less severely. Furthermore, Pape et al. did not define criteria that must be fulfilled for performing the secondary definitive procedure. Therefore these two trials are not comparable in the authors' opinion.

Since there is still no clear evidence for the superiority of one of the strategies participation in the trial is not associated with an increased risk by itself. If one of the strategies proves superiority the benefit (reducing the organ failure) is evident. The main endpoint is a surrogate endpoint for mortality, i. e. the trial may lead to a definite treatment strategy in patients with multiple trauma lowering the overall mortality. If non-inferiority of the primary internal fixation can be proven, it can be assumed that hospital stay, number of operations etc. are lower in this group, thus lowering the expenses.

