Although mortality would have been the most appreciated endpoint, a trial with mortality as the main endpoint would need approximately 1300 patients per arm. In addition to the fact that such a trial is almost undoable for practical reasons the concentration on mortality does not cover all aspects of the planned intervention since the damage control approach primarily tries to limit the sequelae of the "second hit" by surgical intervention. This is reflected by the measurement of organ failure by appointing maximum values for patients who died. The SOFA score has been developed for the sequential evaluation and description of organ failure and has been shown to be a suitable indicator of prognosis in trauma patients [29].

A significant effect may only be shown in a group of medium probability of death (20-60%), especially concerning maximum SOFA-score, as the type of procedure chosen in patient groups of very high or very low mortality will most likely have only a minimal effect on this endpoint.

Because the most important factors that determine prognosis in multiple trauma patients are considered, a comparison of this heterogenic patient collective is possible.

In the current literature, another facet of the optimal surgical treatment in multiple trauma patients is discussed: Biochemical/immunologic factors. It has been shown that the traumatic tissue damage stimulates a maximal activation of the immune system, which leads to its depletion and debilitation [34-36]. As a consequence of a failing immune system a systemic inflammatory response syndrome (SIRS) or sepsis can occur. Both are potentially life threatening complications, in the course of which all organ systems can be affected [34,37,38].

Some of the best analyzed pro-inflammatory cytokines are tumor necrosis factor (TNF)-α [39,40], and the interleukines (IL)-6 and IL-8 [41-43]. Circulating IL-6 is quickly detectable after trauma [42] and has been shown to correlate with trauma load [44].

But so far, the transfer of results into clinical context and the verification for potential decision making (therapy) with respect to risk reduction during secondary surgical procedures after trauma failed.

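### The cost-effectiveness analysis gives no weight to non-fatal outcomes and leaves ward days outside its cost focus, so it does not match a cost objective that covers morbidity as well as mortality

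*Protocol article*

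**What the plan says.** All references are to the protocol article.

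- **Objectives.** The primary objective asks whether the risk-adapted strategy "leads to an improved outcome with respect to morbidity and mortality and if yes at what costs".
- **Statistical analyses, benefit.** "The results will be reported as a cost-effectiveness analysis using life-years lost as the measure of treatment benefit". No other measure of benefit is named for the economic analysis. The results are to feed decision-analytic models of optimum management.
- **Statistical analyses, costs.** "The hospital perspective on costs includes the initial and all secondary operations or readmissions until one year after randomization". The next sentence narrows the work. The reason given is "As most costs during hospital stay are caused by surgery itself and ICU care", and the consequence is that "data collection and statistical analysis will focus on these two aspects".
- **Adverse events.** Damage control is expected to carry more infection, longer ventilation and some failed conversions, "resulting in a higher rate of pseudarthrosis, worse functional result, delayed weight bearing and lower quality of life". Primary nailing is linked to higher mortality and to more, and longer, SIRS, sepsis and multi-organ failure.
- **Discussion.** If primary nailing proves non-inferior, "it can be assumed that hospital stay, number of operations etc. are lower in this group, thus lowering the expenses".
- **Secondary endpoints.** Length of ICU stay, length of hospital stay, pseudarthrosis, function (discharge, 6 and 12 months) and quality of life (6 and 12 months) are all recorded. None is tied to the economic analysis.

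**The concern.** The protocol describes a trade-off. Damage control may reduce organ failure and death at the price of a second operation, a longer stay and poorer recovery of the limb. An economic analysis of that trade-off has to register both sides. A benefit measure that counts deaths alone scores a survivor with a non-united femur and poor function the same as one who has fully recovered. A cost measure centred on surgery and intensive care gives little or no place to a component that the protocol itself expects to differ between the arms.

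What is at stake is the cost part of the primary objective and the management models built on it. A reader could take the cost-effectiveness result as a verdict on the whole trade-off when it covers only part of it.

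**Working it through.** The document gives no economic figure to reproduce, so the check sets the outcomes and resources the protocol expects to differ against what the planned analysis would count.

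| Item | Expected to be worse with | Counted in life-years lost? | In the stated cost scope? |
|---|---|---|---|
| Death | primary nailing | yes, in full | not applicable |
| Survived SIRS, sepsis, organ failure | primary nailing | no | yes, through ICU care |
| Pseudarthrosis, infection (survived) | damage control | no | yes, if it leads to reoperation or readmission within one year |
| Poorer function, delayed weight bearing, lower quality of life | damage control | no | not in themselves |
| Second operation, longer ventilation and ICU stay | damage control | not applicable | yes |
| Ordinary ward days | damage control (longer hospital stay) | not applicable | outside the stated focus |

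**Benefit side.** The objective has two components, morbidity and mortality, and life-years lost carries only the second. The omission affects both arms: non-fatal harms of damage control and survived organ failure after primary nailing both get weight zero.

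**Cost side.** Write the cost difference (damage control minus primary nailing) as

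ΔC = ΔC(surgery) + ΔC(ICU) + u × ΔW,

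where u is the cost of a ward day and ΔW the difference in mean ward days. The stated focus covers the first two terms. The reason given for it concerns the share of *total* cost due to surgery and ICU care, and no figure is attached. A comparison depends on the *difference* between arms, and a component that is small in total can still differ. If ΔW is positive, as the Discussion implies, leaving out u × ΔW understates the cost of damage control. With 70 patients per arm, each day of mean difference is 1 × 70 = 70 ward days in that arm.

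**Direction and size.** Suppose damage control brings a longer ward stay (ΔW > 0) and more non-fatal limb harm than the nailing arm's survived organ failure offsets. Both omissions then favour damage control. The size needs u, ΔW, a weight for non-fatal states and a life expectancy, and the article gives none of these.

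**Can the gap be filled from planned data?** Ward days = length of hospital stay − length of ICU stay, and both are secondary endpoints. Function, quality of life and pseudarthrosis are also recorded.

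**The case against.** The strongest defence has four parts.

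1. *The cost scope is wider than it looks.* The text says focus, not exclusively, and it includes all secondary operations and readmissions to one year. The main extra costs of damage control (the second operation, longer ICU stay, any reoperation for infection or non-union) therefore count against it. This stands. A reader might infer that only surgery and ICU care are costed, or that the harms of damage control are left out altogether. The document does not support either reading. What remains is the ward stay on the cost side and the non-fatal outcomes on the benefit side.
2. *A bias toward damage control is not shown.* A reader might infer that the result favours damage control by construction. It does not. Without a survival gain, the planned analysis would show an arm with an extra operation, more ICU time and no benefit. Survived organ failure, which is linked to nailing, is unweighted too. The direction is conditional on the protocol's own expectations.
3. *The outcomes are reported elsewhere.* All secondary endpoints are to be considered in exploratory analysis, so morbidity is not ignored by the trial. This stands, but nothing places those results beside the costs, which is what the objective asks for.
4. *Life-years is a legitimate choice, and an article condenses.* Choosing life-years over a quality-weighted measure is debatable and not an error, and unit costs belong in the full plan. The point here, however, is about rules the article does state: the benefit measure and the cost focus, set against the objective.

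A further tempting argument is imprecision. The Discussion says "a trial with mortality as the main endpoint would need approximately 1300 patients per arm", against 70 here. With an assumed mortality m of 20% to 60%, the 95% half-width for a mortality difference is 1.96 × √(2m(1 − m)/70), about 13 to 17 percentage points. That is wide, but it is not a reason to reject life-years. The 1300 refers to mortality as the main endpoint, the economic work is to use decision-analytic models, and a quality-weighted measure with death scored zero would carry the same mortality noise.

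**Conclusion.** The mismatch is real and lies in what the article states. The cost objective covers morbidity and mortality. The only stated benefit measure covers mortality, and the cost focus passes over ward days although the Discussion counts hospital stay among the expected savings with primary nailing.

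The planned result would favour damage control if its expected longer stay and non-fatal harms occur and are not offset by survived organ failure in the nailing arm. That direction rests on the protocol's hypotheses and has not been demonstrated. Its size cannot be derived from the document.

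The primary comparison of maximum SOFA score is unaffected. The change is worth making because a stated objective would otherwise be answered only in part, although the trial already records most of what is missing.

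**What to change.** 1. Cost all inpatient days, ICU and ward, taking ward days as recorded hospital stay minus recorded ICU stay, and add them to the surgery, reoperation and readmission costs already planned.
2. Keep the life-years result, and report beside it a cost-consequence table by arm: total cost, survival, function, quality of life at 6 and 12 months, and pseudarthrosis.
3. State in the text that life-years lost gives no weight to non-fatal outcomes in either arm.

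**Cost.** A change of analysis wording and one table. One ward-day unit cost must be assumed, so show the result over a range of values. The 6- and 12-month columns depend on completeness of follow-up, which should be shown by arm. The table avoids turning the quality-of-life instrument into utilities, but it gives no single summary ratio for morbidity and leaves the weighing of outcomes to the reader.

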#### Trial Steering Committee

The Trial Steering Committee will monitor and supervise the trial and comment on any proposed major protocol amendments (see Acknowledgements).

#### Data safety monitoring board

The data safety monitoring board (DSMB) will ensure the safety of the trial.

#### Trial-supporting facilities

The Coordinating Center for Clinical Trials Cologne (KKSK) will provide the infrastructure for data management and internet randomization.

Statistical analysis will be performed in collaboration with the Institute for Operative Medicine (IFOM) at the University of Witten-Herdecke.

The trial is financially supported by the Deutsche Forschungsgemeinschaft (DFG) [grant number: RI 929/3-1].

### Trial documentation and data collection

Electronic case report forms (eCRF) will be used for documentation. However, quality of life and other self rating parameters are regarded as source data and will only be contained in paper based CRF.

### Quality assurance/Monitoring

In order to guarantee a high quality of the study and data retrieval, all participating centers will be visited on a regular base on site by monitors. Data protection rights will be respected. Randomly selected patients files will be analyzed to control original data and to verify accurate data registration and management (100% source data verification in 15% of the patients). The presence of a written informed consent form and the correct interpretation of inclusion and exclusion criteria will be controlled in all patients. The monitor will particularly concentrate on adverse events, the number of drop-outs, and excluded patients. The investigators in the participating centers will support the monitor in his/her activities.

The steering committee or its designees (clinical monitors) may visit participating centers to control adherence to the protocol. Surgical procedures may be evaluated by the Steering Committee, the DSMB or qualified personnel assigned by it.

The database will be checked for faults and validated by the database programmer. Thereafter the database will be approved for data entry (including full audit trail). Complete and incremental data backup will be performed regularly.

### Ethical consideration

The pros and cons of both treatment principles have been discussed above. Clear evidence for the superiority of one of the strategies does not exist. Nowadays, patients with multiple trauma are treated either with primary external fixation or primary internal nail fixation in the sense of early total care or risk adapted damage control. Which of these two principles will be performed often depends on the general hospital strategy. To give a clear cut picture: which treatment will be applicated depends on the hospital the patient enters by chance, the surgeon on duty by chance, as well as patient characteristics.

Participating centers must be trauma level I centers with great experience in multiple trauma care. Both strategies must be established in the hospital, the operating surgeon must be experienced in both strategies as well. Only patients are enrolled in whom both strategies can be performed and only if the surgeon is capable to perform both strategies in this particular patient. The surgeon is allowed to switch the treatment if there are technical or medical reasons for this.

### Ethics Committee (EC) or Institutional Review Board (IRB)

The final study protocol, including the final version of the written informed consent form, was approved by the ethics committee of the University of Cologne, who is responsible for the Clinical Principal Investigator before commencement of the study.

### Ethical Conduct of the Study

The study is conducted according to ICH-GCP (International Conference on Harmonisation for Good Clinical Practice in clinical research), as set out in the European Union Clinical Trials Directive (2001) and associated UK Regulations (2004), which adhere to the principles of the Helsinki Declaration.

Particular aspects are the study protocol, patient information sheet, informed consent form, submission to EC, administrative documents, data registration, registration of adverse events, preparation for inspection and internal audit by authorized personal or the DSMB, and storage of study documents.

Before inclusion (i. e. before randomization or any other study specific procedure is undertaken), patients will be informed about the trial. However, it is expected that at time of admission, the majority of patients suitable to participate in this trial will not be able to give consent due to the severity of their injuries and/or the nature of prehospital therapy (i.e. intubation). If this situation occurs, informed consent could only be obtained from the patient's legally authorized representative. In the event that the patient's legally authorized representative is not available, the patient can be enrolled under waiver of informed consent. This way of enrollment requires a "Physician Authorization Form", where an independent physician and an impartial witness confirm by signature that all above-mentioned regulations were adhered to. The waiver of informed consent also requires that there is no clue either from the patient's side or from the family members objecting against trial enrollment. The Physician Authorization Form will also be signed by the investigator.

This process of enrollment using the waiver of informed consent is in accordance with German law and international standards of research. Due to the urgency of surgical treatment, it is not possible to obtain informed consent from a legal representative appointed by jurisdiction (i.e. Vormundschaftsgericht). It also is impossible to inform the general public about the trial through public notifications.

The patient will be informed about the trial as soon as possible and will be asked to sign the applicable informed consent form to continue participation in the trial. This consent (or its withdrawal thereof) supersede the authority of any previous authorization for trial enrollment.

Patient information will be updated if new relevant information gets available changing the risk-benefit assessment. Patients already enrolled into the study will be informed by the investigator especially if patient's safety is concerned.

The patient will not pay any costs attributed to the type of procedure or investigational device.

